### Analysis

We will present participants’ age, sex, and highest level of education attained as frequencies and proportions.

For the primary and secondary outcomes, we will use fixed-effect models with the stratification variable (education) modelled as a fixed effect, using logistic regression for dichotomous outcomes, linear regression for continuous outcomes and Poisson regression for count outcomes. For the questions that assess applied knowledge or understanding, missing values will be counted as ‘wrong’ answers.

We will report the proportion (for dichotomous outcomes), mean and standard deviation (for continuous outcomes), or median and interquartile range (for count outcomes) in each group, the estimated difference, the estimated confidence interval for the difference, and the *P* value for the difference between groups from the statistical model for each of the primary and secondary outcomes. For attitudes and intended behaviours (Additional file 3), we will dichotomise each outcome by combining, for example, ‘very unlikely’ with ‘unlikely’ and as ‘likely’ with ‘very likely’; and we will report the proportion in each of the four categories.

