### Random allocation

#### Methods for stratification and randomisation

We will stratify our sample proportionately by the highest level of education attained (primary school and below, secondary school, or tertiary education) and whether their children are in a school that is in the intervention or control arm of the IHC primary school resources trial.

We will use computer-generated blocked randomisation. A statistician or other senior researcher at the clinical trials unit at the College of Health Sciences, Makerere University who is not a member of the IHC research team will generate the allocation sequences for the two comparison groups. A web-based random number generator at www.sealedenvelope.com will be used to obtain random permuted blocks with varying block sizes of 4 and 6, and equal allocation ratios, both within blocks and within strata, as shown in Table 1 below.

**Table 1 Tab1:** Excerpt from a sample randomisation list^a^

Column 1	2	3	4	5	6	7
Block identifier	Block size	Sequence within block	Allocation group	Education stratum	Number within stratum	Study code
1	4	1	Group A	≤ primary	1	YL9
1	4	2	Group A	≤ primary	2	PX5
1	4	3	Group B	≤ primary	3	JP3
1	4	4	Group B	≤ primary	4	OB2
2	4	1	Group A	≤ primary	5	XD6
2	4	2	Group A	≤ primary	6	JD0
2	4	3	Group B	≤ primary	7	NU5
2	4	4	Group B	≤ primary	8	SS0
3	4	1	Group B	≤ primary	9	SK0
3	4	2	Group A	≤ primary	10	QN4

^a^List generated from www.sealedenvelope.com

As shown in Table 1 above, the list will have study codes that are unique for each participant (column 7), against which we will attach an ordered array of numbers (column 6) spanning the full breadth of our sample size within each stratum. Each study code will be printed on a separate opaque envelope.

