#### Methods for allocation concealment

The allocation group corresponding to each study code will be printed on a separate slip, inserted and sealed in the corresponding opaque envelope. As shown in the list above, the first participant to be recruited among those with primary or no education will have the study code YL9 on their envelope, inside of which will be a small note with their allocation group (group A).

To reduce the risk of bias during allocation a separate list containing the study participant number, and corresponding study code and number within each stratum, will be generated for each of the three education-level strata (up to and including primary, at least secondary and tertiary), as shown in Table 2 below. This list – which will not identify the study arm – will be given by the statistician to a research assistant who will be in charge of group allocation.

**Table 2 Tab2:** Sample participant recruitment lists for each stratum

Stratum 1: Primary school and below		Stratum 2: At least secondary school		Stratum 3: At least tertiary education	
Number within stratum	Study code	Number within stratum	Study code	Number within stratum	Study code
1	YL9	1	FO4	1	TH4
2	PX5	2	HG6	2	UW0
3	JP3	3	GS3	3	AT5
4	OB2	4	PS9	4	SX4
5	XD6	5	YE9	5	UJ7
6	JD0	6	BH7	6	XD9
7	NU5	7	HN6	7	RJ7
8	SS0	8	TY7	8	CS1
9	SK0	9	DT3	9	BC4
10	QN4	10	FZ1	10	ED1

Upon completion of procedures for confirming consent of a willing participant the research assistant responsible for recruiting the participant will call the research assistant in charge of group allocation. The research assistant responsible for allocation will then open the next available envelope in the stratum, corresponding to the participant’s education level and study arm of the child’s school, to determine the study group to which the parent will be allocated.

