#### Subgroup and exploratory analyses

Education might affect people’s ability to understand and apply the concepts and to answer questions in the Claim Evaluation Tools. We will explore whether there are differences in the effects of the intervention for participants with primary school education versus secondary school education versus tertiary education. We will conduct tests for interaction for the primary outcomes, and we will use published guidelines to interpret the results of these subgroup analyses [41], using the models described above.

The children of all participants will be participating in a parallel trial evaluating the effects of IHC teaching resources, designed to teach P.5 school children concepts that they need to understand and apply to assess treatment claims [34], but only half of them will be receiving the IHC teaching resources. By testing for interaction between IHC teaching resources and the podcast in the statistical models described above we will evaluate whether the combination of the podcast and the IHC teaching resources improves outcomes among parents, compared to the podcast alone.

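### Allocation is stratified by education and by the child's school trial arm, but the outcome models adjust for education only: a small, conservative loss that one sentence would remove

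*Protocol article*

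**What the plan says.** The protocol article describes the strata in three places, and they do not agree.

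- *Methods for stratification and randomisation* gives two factors. The first is education in three levels: "We will stratify our sample proportionately by the highest level of education attained". The second is "whether their children are in a school that is in the intervention or control arm of the IHC primary school resources trial". Three levels by two arms makes six strata. Allocation uses "random permuted blocks with varying block sizes of 4 and 6, and equal allocation ratios, both within blocks and within strata".
- *Methods for allocation concealment* applies both factors when an envelope is opened, the stratum being the one "corresponding to the participant’s education level and study arm of the child’s school". The same section says that the recruitment list "will be generated for each of the three education-level strata". Tables 1 and 2 likewise show education alone.
- *Analysis* recognises one factor: "we will use fixed-effect models with the stratification variable (education) modelled as a fixed effect". It goes on to specify "using logistic regression for dichotomous outcomes, linear regression for continuous outcomes", for the primary and secondary outcomes alike.

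School arm enters the analysis only under *Subgroup and exploratory analyses*: "By testing for interaction between IHC teaching resources and the podcast in the statistical models described above".

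**The concern.** Permuted blocks within strata balance the two podcast groups on school arm. If school arm also predicts parents' scores, the estimated mean difference varies less from trial to trial than a model without school arm assumes. That model leaves the between-arm variance in its residual. For a linear model, the reported standard error is then too large and the test runs below its nominal 5%.

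A link between school arm and parents' scores is plausible on the protocol's own terms. The children's resources teach related concepts, and the investigators both stratify on school arm and plan to ask whether it modifies the podcast effect. About half the selected schools come from each arm (*Sampling technique*), and a binary factor contributes most variance near an even split.

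This is not a detail left to an analysis plan. The article fixes the covariate set, and does so by describing the design as having a single stratification variable.

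**Working it through.** **Inputs.** From the protocol: two stratification factors, blocks of 4 and 6 with 1:1 allocation, school arm roughly 50:50, 397 analysed participants, and a control pass rate of 10% against 20%. The protocol gives no figure for this point that could be reproduced, and none for the effect of school arm on parents. That effect is assumed: a shift *d* of 0 to 0.5 SD in score, with larger values shown only to trace the trend.

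**1. Mean score (linear model).** A balanced binary factor that shifts the mean by *d* residual SDs adds *d*²/4 to the residual variance when it is omitted.

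SE ratio = √(1 + *d*²/4)

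| *d* (SD) | SE ratio | Share of variance, (*d*²/4)/(1 + *d*²/4) |
|---|---|---|
| 0 | 1.000 | 0% |
| 0.2 | 1.005 | 1.0% |
| 0.3 | 1.011 | 2.2% |
| 0.5 | 1.031 | 5.9% |
| 1.0 | 1.118 | 20% |

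Type I error at *d* = 0.5: 2 × (1 − Φ(1.96 × 1.031)) = 4.3%.

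**2. Difference in pass proportions.** With a 10% pass rate overall, the variance without school arm is 0.10 × 0.90 = 0.0900. Within school arms it is the average of the two binomial variances.

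- Pass rates 8% and 12%: (0.0736 + 0.1056)/2 = 0.0896; SE ratio √(0.0900/0.0896) = 1.002.
- Pass rates 5% and 15%: (0.0475 + 0.1275)/2 = 0.0875; SE ratio √(0.0900/0.0875) = 1.014.

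**3. Simulation.** 397 participants, 4,000 runs per scenario, blocks of 4 and 6 within six strata, and an assumed education mix and education effect. The podcast effect was 0.3 SD on the score and an odds ratio of 2.25 on passing, since (0.20/0.80)/(0.10/0.90) = 2.25. Both models were fitted to the same data. Results at *d* = 0.5, taken as a school log odds ratio of 0.91 for passing:

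| Quantity | Education only | Education + school arm |
|---|---|---|
| Linear, no effect: empirical SE | 0.0996 | 0.0996 |
| Linear, no effect: mean model SE | 0.1035 | 0.1004 |
| Linear: type I error | 0.042 | 0.048 |
| Linear: power | 0.826 | 0.838 |
| Logistic: mean log odds ratio | 0.795 | 0.820 |
| Logistic: mean model SE | 0.290 | 0.295 |
| Logistic: power | 0.801 | 0.812 |

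The Monte Carlo error of a type I rate is about √(0.05 × 0.95/4000) = 0.003. The simulated rates therefore agree with the analytic 4.3% but do not refine it.

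The linear rows show the mechanism. The estimate is equally stable under either model, and only the reported standard error differs: 0.1035/0.1004 = 1.031, as in step 1. The logistic rows differ in kind. The standard error is slightly smaller without school arm, but the estimate is attenuated by more, so power drops by 0.812 − 0.801 = 0.011. At a school log odds ratio of 0.36 (*d* = 0.2), logistic power is 0.810 against 0.812.

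Only the contrast between the two models matters here. Whether 397 participants give the power stated under *Sample size* is a separate question.

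**The case against.** The strongest objection is to the premise. *Methods for allocation concealment* and Tables 1 and 2 show lists by education alone. If allocation really ran on three lists, education would be the only stratification variable, the Analysis sentence would be right, and the argument for a below-nominal type I error would fall. This stands as a reason to reconcile the sections. It does not clear the Analysis section, because the stratification text and the envelope instruction both name school arm.

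The second objection is size. The effect of school arm on parents would be indirect, passing from child to parent, and *Outcome assessment* says that pilot parents given the intervention did only slightly better than controls. Zero must be inside the assumed range, and at zero nothing is lost. This stands.

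Three stronger readings are tempting but unsupported:

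- A reader might infer that standard errors are too wide for every outcome. The first primary outcome, passing, is analysed by logistic regression, where omitting a prognostic factor does not widen the standard error of the log odds ratio.
- A reader might multiply 397 by the linear-model variance shares at 0.3 and 0.5 SD and report 9 to 23 participants wasted. But 397 was set for the pass proportion. The ratios in step 2 give 397 × (1 − 0.0896/0.0900) ≈ 2 to 397 × (1 − 0.0875/0.0900) ≈ 11.
- A reader might infer that the school-arm interaction will be fitted without a school-arm main effect. The text does not say so, and including main effects is ordinary practice. Wording that refers back to models without school arm merely leaves it unstated.

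**Conclusion.** The mismatch is real: two factors define the strata, but one is named and modelled. Its consequence is small and conservative.

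For an assumed school-arm effect of 0 to 0.5 SD, the overstatement of the standard error is about 0% to 3% for the mean score. For the difference in pass proportions it is about 0.2% to 1.4% under the assumed pass rates by school arm. For the logistic pass analysis the cost is slight attenuation and, at the upper end, about one percentage point of power.

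These sizes rest on the assumed effect, on a near-even split of participants between school arms, and on allocation having been blocked within school arm as the stratification text states. Validity is not at risk. The case for changing the text is that the correction is free and makes the analysis match the design.

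**What to change.** Replace the model sentence in *Analysis* with, for example: *Education (three levels) and school trial arm (two levels), the two factors that stratify allocation, will be fixed effects in the models for all primary and secondary outcomes; the interaction models will include both main effects.*

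Reconcile *Methods for allocation concealment* and Tables 1 and 2 with the six strata implied by *Methods for stratification and randomisation*. As recruitment is under way, state which lists are actually in use. If they are by education only, correct the stratification text and keep school arm as a prespecified covariate.

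The cost is one sentence, a corrected description of the lists and one extra model parameter. No new data are needed, because allocation already requires the arm of each child's school. The change should be made before the analysis begins.

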#### Subgroup and exploratory analyses

Education might affect people’s ability to understand and apply the concepts and to answer questions in the Claim Evaluation Tools. We will explore whether there are differences in the effects of the intervention for participants with primary school education versus secondary school education versus tertiary education. We will conduct tests for interaction for the primary outcomes, and we will use published guidelines to interpret the results of these subgroup analyses [41], using the models described above.

The children of all participants will be participating in a parallel trial evaluating the effects of IHC teaching resources, designed to teach P.5 school children concepts that they need to understand and apply to assess treatment claims [34], but only half of them will be receiving the IHC teaching resources. By testing for interaction between IHC teaching resources and the podcast in the statistical models described above we will evaluate whether the combination of the podcast and the IHC teaching resources improves outcomes among parents, compared to the podcast alone.

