## Methods

### Study design

This will be a two-arm, parallel-group, individual-randomised trial evaluating the impacts of a podcast series designed to teach concepts of evidence-informed decision-making to parents of primary school children in Uganda (Fig. 1).

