#### Study population and random allocation

Our study population will be parents of primary school children in schools with limited educational and financial resources. We will draw a sample of parents of children from schools participating in a cluster-randomised trial of IHC primary school resources, designed to help primary school children understand and assess claims made about treatment effects [34].

All public and private primary schools in the central region of Uganda will be eligible to participate in the IHC primary school resources trial. The only exclusions will be international schools, special needs children’s schools for the deaf and blind, and schools or classes that participated in the user-testing and piloting of the teaching resources. We intend to include at least 120 schools in that trial.

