### Sampling technique

We will randomly select at least 30 schools among the 120 participating in the related trial evaluating the effectiveness of IHC materials designed for primary school children [34]. This number is informed by findings from our earlier engagements with parents, in which only about 10 to 20 parents attended meetings that are not on the usual school programme. About half of the schools selected will be from the intervention arm and the other half from the control arm of the schools participating in the trial evaluating primary school resources. In each of the selected schools we will create a list of parents of P.5 children and invite them to a meeting at the schools. At these meetings we will provide parents with information about the podcast trial and seek their consent to participate.

Because parents who attend meetings might be different than those who do not, we will also make an effort to reach parents who will not have attended the meetings through phone calls, where possible.

Parents who accept to participate will be asked to sign a Consent Form (Additional files 1 and 2) before randomisation to begin their participation in the study.

We will provide information about the trial to participants in a brochure designed as part of a package inviting parents to participate. This information will also be available on the participants’ Informed Consent Forms and will be written in the two most commonly spoken languages (English and Luganda).

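### The podcast-by-school-resources interaction test does not answer the question set for it, whether podcast plus resources does better than podcast alone (exploratory analysis only)

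*Protocol article*

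**What the plan says.** Under Subgroup and exploratory analyses, one sentence of the protocol article gives both a method and a purpose. The method is "By testing for interaction between IHC teaching resources and the podcast in the statistical models described above". The purpose is that "we will evaluate whether the combination of the podcast and the IHC teaching resources improves outcomes among parents, compared to the podcast alone".

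The paragraph before it also uses an interaction test, for education. There the purpose is to see whether the podcast's effect varies by education level, and test and purpose match.

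The models referred back to are in the Analysis section: "we will use fixed-effect models with the stratification variable (education) modelled as a fixed effect, using logistic regression for dichotomous outcomes", with linear regression for continuous and Poisson regression for count outcomes. No school term or allowance for clustering is named.

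The two factors are allocated at different levels. For the podcast, Study design says "This will be a two-arm, parallel-group, individual-randomised trial evaluating the impacts of a podcast series". For the resources, Study population and random allocation says "We will draw a sample of parents of children from schools participating in a cluster-randomised trial of IHC primary school resources". Under Sampling technique, "We will randomly select at least 30 schools among the 120 participating in the related trial", and "About half of the schools selected will be from the intervention arm and the other half from the control arm".

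**The concern.** The purpose names a comparator, podcast alone. It therefore asks for a difference between two of the four groups in the 2 × 2 layout: both interventions against podcast only. An interaction uses all four groups and asks whether the podcast does more, or less, in resource schools than in control schools.

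If the plan is followed literally, a null interaction could be reported as no gain from adding the school resources when there is one. A significant interaction could likewise be read as an answer to the stated question when the combination equals podcast alone.

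A second matter arises only on repair. The contrast that answers the question compares parents in different schools, and those schools were randomised as clusters.

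**Working it through.** The article gives no figure for this analysis, so there is none to reproduce. The numbers of parents (397 analysed, 497 recruited) are taken as given from the Sample size section, and their derivation does not matter here.

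**1. The two quantities.** Write 00 for neither, P for podcast only, R for resources only and PR for both.

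- Stated question: PR − P = school-arm coefficient + interaction.
- Stated test: (PR − R) − (P − 00) = interaction alone.

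**2. Illustration on pass rates.** 00 = 10% is the article's assumed control rate, and P = 20% adds its 10-point target difference. The R and PR rates are assumptions. The podcast odds ratio in control schools is (0.20/0.80)/(0.10/0.90) = 2.25. The last column divides the podcast odds ratio in resource schools by 2.25.

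| 00 | P | R | PR | PR − P (points) | Interaction (points) | Ratio of odds ratios |
|---|---|---|---|---|---|---|
| 10% | 20% | 15% | 25% | +5 | (25−15)−(20−10) = 0 | 1.889/2.25 = 0.84 |
| 10% | 20% | 20% | 30% | +10 | (30−20)−(20−10) = 0 | 1.714/2.25 = 0.76 |
| 10% | 20% | 20% | 36% | +16 | (36−20)−(20−10) = +6 | 2.25/2.25 = 1.00 |
| 10% | 20% | 20% | 20% | 0 | (20−20)−(20−10) = −10 | 1.00/2.25 = 0.44 |

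In the first three rows the combination is better, and the logistic interaction is below or equal to 1. In the last row the combination adds nothing, and the interaction is far from null.

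**3. Illustration on the mean score.** A simulation used 4,000 runs per setting, a linear model with total SD 1, and 30 schools (15 per arm) with 13 analysed parents each (390 in all, close to 397). Parents were randomised individually to the podcast within school arm. The school effect was a random intercept shared by both podcast groups.

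- Resources add 0.4 SD with or without the podcast, so the combination is better. The interaction test rejects in 4.2% to 5.4% of runs (ICC 0 to 0.10). A school-level test of PR − P rejects in 73.2%, 64.4% and 56.1% at ICC 0, 0.05 and 0.10.
- Resources add 0.4 SD without the podcast and nothing with it, so the combination equals podcast alone. The interaction test rejects in 49.6% and 50.6% (ICC 0 and 0.05).

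**4. Clustering, for the replacement contrast only.** Podcast parents per school: 397/2/30 = 6.62, or 497/2/30 = 8.28 with no loss. Design effect = 1 + (m − 1) × ICC. Actual type I error = 2 × [1 − Φ(1.96/√design effect)]. For example, at m = 6.62 and ICC 0.05 the design effect is 1 + 5.62 × 0.05 = 1.28, and 2 × [1 − Φ(1.96/1.13)] = 8.3%. All ICCs are assumed. The simulated columns come from the null version of the simulation above.

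| ICC | Design effect, m = 6.62 | Type I error, m = 6.62 | Type I error, m = 8.28 | Simulated PR − P, no school term | Simulated PR − P, school-level summaries | Simulated interaction, no school term |
|---|---|---|---|---|---|---|
| 0 | 1 | 5% | 5% | 4.7% | 4.2% | 5.3% |
| 0.01 | 1.06 | 5.7% | 5.9% | not run | not run | not run |
| 0.05 | 1.28 | 8.3% | 9.3% | 8.3% | 4.9% | 4.6% |
| 0.10 | 1.56 | 11.7% | 13.6% | 12.3% | 4.4% | 4.8% |
| 0.20 | 2.12 | 17.9% | 21.1% | 17.8% | 4.6% | 4.8% |

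The interaction keeps its size because parents within the same school are randomised to podcast or control, so a shared school effect largely cancels.

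**The case against.** **The authors may have meant effect modification.** The sentence sits among exploratory analyses and names an interaction test straight after a correct one for education. If they wanted to know whether the podcast works better where the child also receives the resources, the test is right and only the closing phrase is loose. This is a fair reading, and on it a rewording is enough. But the comparator as printed is podcast alone, which defines a different quantity, so the text needs changing either way.

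**The illustrations are generous.** The article gives no reason to expect that children's lessons raise parents' pass rates by 5 or 10 points. In the first two rows the negative sign appears only on the logit scale. With about 99 parents per cell (397/4), the variance of the log ratio of odds ratios in the first row is (1/99) × (1/0.09 + 1/0.16 + 1/0.1275 + 1/0.1875) = 0.31. The standard error is thus about 0.55, and the 95% interval around 0.84 is about 0.28 to 2.5. The trial would more likely see an uninformative interaction than a convincing reversal. This limits the practical size of the problem but leaves the mismatch in place.

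**Stronger readings the article does not support.** A reader might infer that clustering invalidates the planned interaction test. It does not do so materially: the podcast is randomised to individuals, and the simulated size stayed at 4.6% to 5.3%. A reader might also infer that the model omits the school-arm main effect because the Analysis section names only education. That section does not list the podcast term either, an interaction test ordinarily carries both main effects, and an article commonly leaves the full formula to a fuller document.

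**Conclusion.** The point holds for one exploratory analysis. The article states a question and a test, and the test does not answer the question. The interaction can be zero or negative when the combination is better, and non-zero when it adds nothing. This follows from the definitions; only the example rates are assumed.

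The clustering part is conditional. It applies if the contrast that answers the question is fitted in the Analysis section's models without allowing for school. Type I error at a nominal 5% would then be about 6% at ICC 0.01 and about 8% to 21% at 0.05 to 0.20, with 30 schools and 397 to 497 parents. More than 30 schools would mean fewer parents per school and less inflation. The finding that the interaction is unaffected assumes a school effect common to both podcast groups.

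It would be wrong to carry this over to the main result. The primary podcast comparison is individually randomised and does not depend on this contrast, which is also absent from the listed objectives.

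**What to change.** - Keep the interaction test and describe it as a test of whether the podcast's effect differs between school arms.
- If the comparison with podcast alone is wanted, pre-specify it separately: the school-arm contrast among podcast parents (school-arm coefficient plus interaction), reported with confidence intervals as a difference in pass proportion and in mean score.
- Fit that contrast with podcast, school arm, their interaction and education, and allow for school through a random intercept, school-clustered standard errors with a small-sample correction (about 15 + 15 − 2 = 28 degrees of freedom), or school-level summaries.
- If only effect modification was intended, reword the closing phrase and omit the contrast.

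This takes a few lines of text. School arm is known for every parent because it is a stratification factor. Parents are recruited through their schools, but the article does not say that a school identifier is held in the analysis dataset, so that should be confirmed. The statistical cost is a wider interval for an exploratory contrast that is already imprecise: for 20% against 30% with 99 parents per cell, power is about 37% ignoring clustering and about 30% with a design effect of 1.28.
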